#### Sample size and power

With an expected peritonitis-related complications rate of 40% in the ROD group [20] and 25% in the VAC group [42, 44], the desired power of 80%, a significance level of 0.05, and an expected drop-out of 5%, a total of 340 patients should be included.

As the CCI distribution in this group of patients is unknown, we could not perform an explicit sample size calculation for this secondary outcome. A 0.32 standard deviation difference in mean CCI between the two groups could be detected with 80% power with this sample size.

To ensure sufficient recruitment, the study will be multicentre and European. Eight active centres have been included, and two are in process. Randomisation tools along with eligibility criteria are accessible through our website. The workflow and relevant contact details appear on posters at the participating departments. Study progress will be available on the website.

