#### Statistical analysis

Patient characteristics will be summarised with frequencies and proportions (for categorical variables) or with mean values ± standard deviation, median values, quartiles, and minimum and maximum values (for numerical variables). Categorical variables will be compared using a Fisher's exact test and continuous variables with a Wilcoxon rank-sum test.

The primary peritonitis-related complication outcome will be compared between intervention groups by the Chi-square test, reported as relative risk with a 95% CI. The CCI outcome will be compared by linear regression with bootstrapped standard errors reporting the mean difference with 95% confidence intervals.

The main analysis will be performed as a superiority analysis of VAC treatment against primary closure with ROD. In addition, a non-inferiority analysis with a margin of 5% will be reported for peritonitis-related complications as a secondary analysis.

A univariate analysis will be performed on the individual complication types (abscess, leakage, etc.) and complications as a whole (peritonitis-related complications and CCI). Fisher's exact or Chi-square test will be used to compare the treatments depending on the number of observations.

Adjusted analysis by logistic regression will be performed for complications as a whole and the individual complications as an outcome, adjusted for age, performance status, and comorbidity. The above analyses will also be performed as a subgroup analysis where patients with APACHE II score > 10 will be included. This evaluates VAC and ROD in the most seriously ill portion of the patient population.

The hospital healthcare utility and average treatment costs are compared between the treatment groups. The resource use will be reported as the mean difference with 95% confidence intervals (CI) compared by linear regression. In case of deviations from normality assumptions, bootstrapping with 1000 repetitions will be performed. Finally, the proportion of patients who experience radiological, acute operations will be compared by binomial regression estimating relative risk (RR) with 95% CI.

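### CCI, which the article analyses as a mean, is also assigned to Fisher/chi-square tests and to logistic regression as its only adjusted analysis, with no cut-point given

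*Protocol article*

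**What the plan says.** All the relevant statements stand in two sections of the protocol article.

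- **Sample size and power** treats CCI as a score with a mean and a standard deviation: "A 0.32 standard deviation difference in mean CCI between the two groups could be detected with 80% power with this sample size". It also says that the distribution of CCI in these patients is not known.
- **Statistical analysis**, second paragraph, gives CCI its own method: "The CCI outcome will be compared by linear regression with bootstrapped standard errors reporting the mean difference with 95% confidence intervals". No covariates are named there.
- **Statistical analysis**, paragraph on univariate analysis, lists the individual complication types and then "complications as a whole (peritonitis-related complications and CCI"). The next sentence reads: "Fisher's exact or Chi-square test will be used to compare the treatments depending on the number of observations". CCI is not excepted.
- **Statistical analysis**, following paragraph: "Adjusted analysis by logistic regression will be performed for complications as a whole and the individual complications as an outcome". The covariates named for this model are age, performance status and comorbidity. The analyses described up to that point are then repeated in patients with an APACHE II score above 10.

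Neither section gives a cut-point for CCI, and neither describes an adjusted linear model for it.

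**The concern.** The parenthesis names CCI expressly, so the conflict does not depend on guessing what the group of overall complications contains. The group holds one binary outcome (the peritonitis-related composite) and one score. The methods assigned to the group suit only the binary outcome.

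This has two consequences. First, CCI has two unadjusted analyses of different kinds, a mean difference and a categorical test, and the second cannot be carried out on the score itself. Second, the adjusted analysis of CCI has only one stated method, and that method needs a binary outcome. Anyone who follows the text must either depart from it or choose a cut-point.

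CCI is the first-listed secondary outcome (Objectives), measured at 30 days, 90 days and one year. The article says that it may be the best measure of postoperative morbidity. The trial is not blinded (Study design). A cut-point chosen once data are at hand would be a choice that the plan leaves open, on an outcome that readers will look at closely.

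**Working it through.** **1. The methods side by side**

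| Analysis of CCI | Method stated | Usable on the score? |
|---|---|---|
| Unadjusted, main | Linear regression, bootstrapped SE, mean difference | Yes |
| Univariate, with the composite | Fisher's exact or chi-square | Only after a cut |
| Adjusted | Logistic regression | Only after a cut |
| APACHE II > 10, unadjusted | Repeats the analyses above, so includes the linear regression | Yes |
| APACHE II > 10, adjusted | Logistic regression | Only after a cut |

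The choice between Fisher and chi-square is tied to the number of observations, not to the type of variable, so that sentence offers no way out for CCI.

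**2. The article's own CCI figure**

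Inputs from Sample size and power: 340 patients, 5% drop-out, significance level 0.05, power 80%, difference 0.32 SD. Assumed: two-sided test, equal arms.

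- Evaluable patients: 340 × 0.95 = 323.
- Power = Φ(d·√N/2 − 1.96) = Φ(0.32 × 17.97/2 − 1.96) = Φ(0.92) = 82%.
- Detectable difference at 80% power = 2.80 × 2/√323 = 0.312 SD. With 304 patients (the uninflated number for 40% against 25%) it is 0.321 SD.

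The stated 0.32 SD is therefore reproduced, slightly on the cautious side. It refers to a comparison of means.

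**3. What a cut-point would cost, assuming a normal score**

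The share of information kept when a fraction q lies above the cut c is φ(c)²/[q(1 − q)].

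- Median split: φ(0)²/0.25 = 2/π = 0.637, so 36% is lost.
- Power at 0.32 SD = Φ(0.32 × 17.97/2 × √0.637 − 1.96) = Φ(0.33) = 63%.
- Detectable difference = 0.312/√0.637 = 0.391 SD.
- Evaluable patients needed for 80% power at 0.32 SD: about 484, against 308 for the comparison of means.

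Other cuts, with 323 evaluable. Power is for comparing the two proportions that result from a 0.32 SD shift:

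| Fraction above the cut | Information lost | Power |
|---|---|---|
| 50% | 36% | 63% |
| 40% | 38% | 62% |
| 30% | 42% | 58% |
| 20% | 51% | 52% |
| 10% | 66% | 38% |

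These figures are for an unadjusted comparison. For the adjusted logistic model they are a guide only.

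**4. Sensitivity to the shape of the distribution**

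Because the article calls the distribution unknown, one skewed case was simulated: a gamma score with shape 2, a location shift of 0.32 SD, 161 patients per arm and 4,000 simulated trials. The t-test had 82% power. Cuts at the 25th, 50th, 75th and 90th percentiles gave 93%, 73%, 40% and 19%. The cost can be nil or far above the normal-theory minimum, depending on a choice that the plan does not make.

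**The case against.** The strongest reply is that this is loose drafting. The only sentence that names CCI alone and gives it a method is the linear regression. Nowhere does the article propose to dichotomise it. A statistician could not run Fisher's test or a logistic model on the raw score and would ask before inventing a threshold. An analysis plan may also settle the adjusted model. It is fair that a post hoc cut-point is a possibility and not an announced intention, and that its effect on type I error has not been quantified. But the point is not that detail is missing. The text states a method that does not fit the variable and that conflicts with its own earlier sentence. A later plan would have to override it.

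Several stronger readings are tempting and are not supported:

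- *The power claimed for CCI is lost.* It belongs to the comparison of means, which stays a linear regression.
- *Logistic regression is the only method for CCI in the APACHE II subgroup.* The subgroup repeats the analyses above it, and these include the unadjusted linear regression. Only the adjusted subgroup analysis is affected.
- *Access to interim results would let the study group pick a favourable CCI cut.* The interim analyses are confined to the 30-day primary outcome, so they give no direct view of CCI. The open design is the only part of this argument that stands.
- *About a third of the information is lost.* That is the figure for a median split of a normal score, not a general one.

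**Conclusion.** The inconsistency is real and can be checked within one section. CCI is placed among outcomes assigned to categorical tests and logistic regression, although the article treats it as a mean everywhere else. As written, the extra univariate test and the adjusted analysis of CCI, overall and in the APACHE II > 10 subgroup, cannot be done without an unstated cut-point.

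The reach is limited. The primary analysis, the main unadjusted CCI comparison, its power statement and the unadjusted subgroup comparison are all intact. Any loss of information falls only on the affected supporting analyses, and only if the score is dichotomised. Its size is conditional: between 36% and about 66% for the cuts examined under normality with 323 evaluable patients, and anything from none to more than that for a skewed score. The wording should be corrected because the outcome is prominent and the correction is nearly free. It does not threaten the trial's main conclusion.

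**What to change.** Three edits in Statistical analysis:

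1. Remove CCI from the parenthesis in the univariate paragraph, so that Fisher's exact and chi-square tests apply to the peritonitis-related composite and the individual complications only.
2. Restrict the logistic regression sentence to those same binary outcomes.
3. Add that the adjusted analysis of CCI, overall and in the APACHE II > 10 subgroup, is a linear regression with bootstrapped standard errors and the covariates already listed (age, performance status and comorbidity), reported as a mean difference with its 95% confidence interval.

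This uses only methods and covariates that the section already contains. It changes a few sentences and needs no new data and no more patients. It should be made before any CCI data are analysed.

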The method with VAC was initially introduced in damage control trauma surgery and has gained increasing use in the treatment of complicated intra-abdominal infections [21, 31–43]. A systematic review and meta-analysis by Atema et al. in 2015 showed an incidence of 14.6% for enteroatmospheric fistula (EAF) and 48.5% for incisional hernias in the group treated with VAC, where 82% of the population was treated for peritonitis. The mortality varied between 21.5 and 30.0%. The VAC procedure can be applied and modified in several ways. The most common are fascial traction methods (mesh mediated or non-mesh mediated), the applied vacuum pressure and the interval for changes of the VAC [42]. The VAC treatment in the present study will be performed with a non-mesh-mediated fascial traction method and narrowing technique. A retrospective study from our institute using this technique, including 115 patients with secondary peritonitis, found a mortality rate of 17% and EAF of 3.5%; secondary closure was obtained in 92% of the patients [44].

The present study will aim to compare the postoperative results of ROD and VAC in patients with secondary peritonitis by a randomised controlled trial with peritonitis-related complications as the primary outcome; comprehensive complication index (CCI), mortality, quality of life, the development of incisional hernia, and hospital care utility and costs were the secondary outcomes.

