The interim analysis will be performed at 25%, 50%, and 75% of recruited patients on the primary outcome after 30-days to detect significant differences between groups at the earliest possible time, ultimately leading to the termination of the study. We have adjusted our power calculation to the interim analyses using the O'Brien–Fleming method. The study group will have access to the results of the interim analyses and may make the final decision to terminate the study.

All of the above analyses will be performed as both intention-to-treat (patients will be analysed according to their randomisation group) and per-protocol analysis (what actually happened). The main analyses will be performed as complete case analyses. Multiple imputations will impute missing values in a supplementary analysis, including baseline characteristics as predictors.

*P* values < 0.05 will be considered statistically significant. Statistical calculations will be performed using Stata software (version 15, Stata Corp LP, Texas, USA).

In the VACOR-Microdialysis sub-study, the parameters will be compared using descriptive statistics for continuous and discrete variables. Repeated measurement across time points will be compared by mixed-effects regression models, including the interaction between time points and operation method and a random intercept for each patient. In addition, normality assumptions will be graphically assessed using quantile–quantile plots.

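### Logistic regression is fixed for every individual complication, with no sparse-data form, so rare items may have no finite adjusted odds ratio (minor)

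*Protocol article*

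**What the plan says.** All references are to the protocol article.

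- **Adjusted model** (Statistical analysis): "Adjusted analysis by logistic regression will be performed for complications as a whole and the individual complications as an outcome". The covariates are age, performance status and comorbidity. The type of logistic regression (maximum likelihood, penalised or exact) and the test are not stated.
- **Unadjusted comparison of the same items** (Statistical analysis): "Fisher's exact or Chi-square test will be used to compare the treatments depending on the number of observations". This comparison therefore has a rule for small counts.
- **Repeats** (Statistical analysis): "The above analyses will also be performed as a subgroup analysis where patients with APACHE II score > 10 will be included", and "All of the above analyses will be performed as both intention-to-treat" as well as per protocol.
- **Outcomes** (Table 1): 8 non-surgical and 12 surgical items, 20 in all. Fistula is in both lists and covers connections to skin, to the outside, or between two hollow organs.
- **Departures from allocation** (Randomisation): in some situations VAC may be used whatever the allocation, and the patient stays in the analysis.
- **Fistula after VAC** (Background): the lead centre's retrospective series "found a mortality rate of 17% and EAF of 3.5%; secondary closure was obtained in 92% of the patients"; the cited meta-analysis gives 14.6%. No rate is given for ROD.

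**The concern.** One model is fixed for outcomes with very different event counts. The composite will have ample events. Single items such as urosepsis, compartment syndrome or fistula may have a handful, or none in one arm. With an empty arm, the likelihood keeps rising as the treatment coefficient moves to plus or minus infinity. Software then reports a meaningless estimate with a huge standard error, or drops the term. With one or two events in an arm an estimate exists, but its standard error is so large that a Wald test rarely rejects.

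At stake are the adjusted odds ratio and interval for the rare complications, which include some that the Background and Discussion name as reasons to prefer one strategy. If the difficulty is first met when the tables are built, the substitute method is chosen with the counts in view, in a trial that is not blinded.

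**Working it through.** **Arm size.** Sample size and power gives 40% against 25%, 80% power, 5% significance, 5% drop-out and a total of 340. A two-sided two-proportion formula with continuity correction gives 165 per arm, 330 in total, and 330/0.95 = 347.4, so 348, within 3% of 340. Without the correction it gives 152 per arm, 304, and 320 after drop-out. The point does not rest on this; it only sets the arm size: 340 × 0.95 = 323, about 161 per arm.

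**Chance of an empty arm.** P(no events) = (1 − p)^n. The rates p are assumptions, because the article gives none by item and arm. The subgroup sizes are also assumed.

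| True rate in the arm | n = 161 | n = 80 | n = 40 |
|---|---|---|---|
| 0.5% | 45% | 67% | 82% |
| 1% | 20% | 45% | 67% |
| 2% | 3.9% | 20% | 45% |
| 3.5% | 0.3% | 5.8% | 24% |

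**Across Table 1.** "With an expected peritonitis-related complications rate of 40% in the ROD group" gives 161 × 0.40 = 64 affected patients; 25% under VAC gives 161 × 0.25 = 40. As an illustration, assume that events spread evenly over 20 independent Poisson items.

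- One item per affected patient: 64/20 = 3.2 and 40/20 = 2.0 events per item. P(at least one arm empty) = e^−3.2 + e^−2.0 − e^−5.2 = 0.041 + 0.135 − 0.006 = 0.171 per item. That is 20 × 0.171 = 3.4 items, with about a 97% chance of at least one.
- Two items per patient: 0.4 items (33%) in the full trial. A subgroup of half the patients returns to 3.2 and 2.0 per item, so 3.4 items (97%).
- Three items per patient: 5% in the full trial, 69% in that subgroup.

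An uneven spread would leave the rarer items sparser still.

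**What the model does with an empty arm.** Take 6/161 against 0/161 (161 × 0.035 = 5.6) with three simulated covariates.

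| Newton-Raphson iterations | Treatment log-odds ratio | Standard error |
|---|---|---|
| 10 | 7.9 | 13 |
| 20 | 17.9 | 1,904 |
| 30 | 27.9 | 282,690 |

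The estimate diverges. A Firth-penalised fit to the same data gives log-odds ratio 2.56 (standard error 1.33), an odds ratio of e^2.56 = 12.9. Fisher's exact test, already planned, gives p = 2 × C(161,6)/C(322,6) = 0.030.

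**Power when counts are small.** Simulation with 161 per arm and assumed log-odds slopes of 0.4 (standardised age), 0.3 (performance status 0 to 3) and 0.15 (comorbidity count); an empty arm counts as no rejection for the Wald test.

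- At 0.5% against 3.5%, the model is non-estimable in about 45 to 48% of trials. Power is 6 to 9% (Wald), 29 to 30% (Fisher) and 49% (Firth likelihood ratio).
- At 2% against 8%, the gap is small: 66% (Wald) against 74% (Firth).
- With equal rates of 1 to 2%, the Firth test rejects in 3 to 4% of trials, so its advantage is not bought with excess false positives.

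**The case against.** **This is detail for the analysis plan.** A sparse-data fallback for secondary adjusted models is often left to a plan that is not shown here. That limits the weight of the point. It does not remove it: the article does not leave the model open, but names one for every item, and for the rare items the plain reading of that model cannot deliver an adjusted estimate.

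**Maximum likelihood and the Wald test are inferred.** This is correct. Unqualified logistic regression is normally fitted by maximum likelihood, but the text does not exclude a penalised fit and names no test. The low Wald power is not a property of logistic regression as such. An unpenalised likelihood-ratio test can be computed with an empty arm and had 59% power at 0.5% against 3.5%. It was liberal, however, rejecting in about 6 to 9% of trials at equal low rates, and it leaves the odds ratio infinite.

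**Fistula need not be the failing case.** A reader might infer that the adjusted analysis is bound to fail on fistula because it is a harm of the open abdomen. The documents do not support that. Table 1 fistula includes types that can follow primary closure, and ROD patients may receive VAC and stay in the intention-to-treat set. At a ROD rate of 3.5%, the chance of no ROD fistula is 0.3%.

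**The harm signal survives.** A reader might also infer that an excess of a rare harm would be hidden. It would not: the Fisher comparison is valid in a randomised trial and works with an empty arm (6 against 0, p = 0.030).

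**Conclusion.** The point holds as a minor one. Read plainly, the stated adjusted model gives no finite odds ratio for any complication with an empty arm, and a weak Wald test where an arm has very few events. Such items are plausible in the full trial and more likely in the APACHE II subgroup. The chance for a given item runs from about 45% at a 0.5% arm rate to 0.3% at 3.5% with 161 per arm, and from 67% to 5.8% with 80 per arm. These figures rest on assumed item rates and an assumed subgroup size. The power figures rest further on a Wald test and assumed covariate effects. Fistula is one possible example, not an established failure. The primary Chi-square analysis, the adjusted composite model (about 64 and 40 affected patients expected) and the unadjusted item comparisons stand as planned.

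**What to change.** In Statistical analysis, separate the individual complications from the composite, for example: *Individual complications will be analysed by Firth penalised-likelihood logistic regression, with profile penalised-likelihood confidence intervals and penalised likelihood-ratio P values, adjusted for age, performance status and comorbidity. The same applies in the APACHE II subgroup and in the per-protocol analysis. The composite will be analysed by ordinary logistic regression.*

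A narrower version would also do: use the Firth model only for items with few events in either arm, under a count threshold fixed before the data are seen.

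The cost is one sentence and a user-written Stata command. Firth odds ratios are shrunk slightly towards 1 and are less familiar to readers. No extra patients or data are needed.

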### Preoperative patient assessment

The patients are preoperatively assessed according to Sequential Organ Failure Assessment (SOFA) to determine the degree of organ dysfunction [46].

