### Postoperative patient assessment

Immediately after index operation, the surgeon fills out the baseline form containing patient characteristics, Charlson comorbidity index, aetiology and extent of the peritonitis, surgical procedure, Mannheims peritonitis index and classification of the OA according to Bjork's classification [48, 49]. Patients can be transferred postoperatively to the intensive care unit (ICU) or the ward at the discretion of the treating team. Upon arrival to either the ward or the ICU, Acute Physiology and Chronic Health Evaluation II (APACHE II) score must be obtained by the attending anaesthesiologist [46, 50]. SOFA-scoring and routine blood samples with CRP, bilirubin, creatinine, and platelets must be performed daily within the first seven days after index operation. Discharge from the ICU will be at the discretion of the attending intensivist and surgeon.

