#### Data collection and participant timeline

The pre- and perioperative assessment will consist of: baseline data (sex, age, surgery date, height, weight, body mass index, ASA score, WHO performance score, smoking, alcohol consumption, presence of comorbidities, previous abdominal surgeries, and steroid use). Data for surgical findings include aetiology of disease, anatomical location of intestinal perforation, degree of contamination, surgical treatment, method of abdominal wall closure, and suture material used for abdominal wall closure. Postoperative monitoring consists of SOFA, APACHE II, CRP, VAC treatment duration, unplanned VAC change, and the number of laparotomies in the ROD group. A patient record review will be performed at the follow-up after one month, three months, one year, and five years (Fig. 3). All data will be stored in REDCap®, hosted by the Odense Patient data Explorative Network (OPEN).

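### Preoperative SOFA is scored but named in no analysis, and the fixed covariates of the adjusted complication models contain no measure of acute organ dysfunction

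*Protocol article*

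**What the plan says.** Under Preoperative patient assessment, the protocol article states: "The patients are preoperatively assessed according to Sequential Organ Failure Assessment (SOFA) to determine the degree of organ dysfunction". Under Objectives, SOFA over the first seven postoperative days is a secondary outcome.

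Under Statistical analysis, complications as a whole and individual complications are analysed by logistic regression "adjusted for age, performance status, and comorbidity". Acute severity enters only through a restriction: the same analyses are "performed as a subgroup analysis where patients with APACHE II score > 10 will be included". The timing of that score is given under Postoperative patient assessment: "Upon arrival to either the ward or the ICU, Acute Physiology and Chronic Health Evaluation II (APACHE II) score must be obtained".

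Under Data collection and participant timeline, the pre- and perioperative list includes "surgery date, height, weight, body mass index, ASA score, WHO performance score, smoking, alcohol consumption" but not SOFA. SOFA appears there only later: "Postoperative monitoring consists of SOFA, APACHE II, CRP, VAC treatment duration".

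**The concern.** The Discussion says that patients enter whatever their general condition, so organ dysfunction at the time of surgery can be expected to vary widely. The score that records it before treatment has no named use. The three covariates that were fixed describe age, functional status and comorbidity, not how ill the patient is at that moment.

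APACHE II does not fill the gap. It is scored on arrival at the ward or ICU, when the abdomen has already been closed or the VAC applied, so it is not a clean pre-treatment covariate.

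At stake are the precision of the adjusted complication analyses and their ability to correct a chance imbalance in acute severity. The same applies to any comparison of postoperative SOFA made without its starting value.

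**Working it through.** **What is measured, when, and how it is used**

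| Measure | Timing in the article | Named use in the analysis |
|---|---|---|
| Age, performance status, comorbidity | Baseline | Covariates of the logistic models |
| ASA score | Pre-/perioperative list | None named |
| SOFA, preoperative | Before surgery | None named |
| Mannheim peritonitis index | Form completed just after the index operation | None named |
| APACHE II | Arrival at ward or ICU, after the operation | Subgroup above 10 |
| SOFA, days 1 to 7 | After the operation | Secondary outcome; no method named |

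Preoperative SOFA is thus the only organ-dysfunction score stated as taken before the operation.

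**The plan's own figures.** Sample size and power gives a detectable CCI difference of 0.32 SD at 80% power. For two equal groups with N evaluable patients, the detectable difference is (1.96 + 0.84) × √(4/N).
- N = 304 (152 per arm, the pooled two-proportion result for 40% against 25%): 0.321 SD.
- N = 323 (340 × 0.95): 0.312 SD.

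Both agree with 0.32. The continuity-corrected formula gives 165 per arm, and 330/0.95 = 348, within 3% of the stated 340. Neither the 0.32 SD nor the 340 involves a covariate, so this point moves neither.

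**Illustration for a continuous outcome (r is assumed).** Adjusting for a baseline that correlates r with the outcome multiplies the residual variance by 1 − r², and the detectable difference by √(1 − r²). With N = 323:

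| Assumed r | Fall in variance | Detectable difference |
|---|---|---|
| 0 | 0% | 0.312 SD |
| 0.4 | 16% | 0.286 SD |
| 0.5 | 25% | 0.270 SD |
| 0.7 | 49% | 0.223 SD |

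The article gives no correlation between preoperative SOFA and any outcome, so the table shows a range and not an estimate. The formula holds for a linear model and does not carry over to a log odds ratio. No size can be given for the logistic models from the documents.

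**What missing scores would cost.** If a fraction m of patients lacks preoperative SOFA and is dropped, the variance of the treatment estimate is proportional to (1 − r²)/[N(1 − m)]. The gain is cancelled when m = r². At r = 0.4 that is 16%, or about 52 of 323 patients (0.16 × 323 = 51.7); at r = 0.7 it is 49%. Moderate missingness would therefore not remove the benefit, but it would erode it.

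**The case against.** The strongest case against is that the adjusted models are supplementary and already have three plausible, prespecified covariates, so that a further one is a matter of preference. Randomisation protects the unadjusted comparison, and chance imbalance is already covered by the test's error rate. This stands, and it limits the point to the adjusted analyses. It does not explain why a score already taken before treatment is left out while the only acute score used is a post-operative one.

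The article is also condensed. Preoperative SOFA could be among the generic baseline summaries ("Patient characteristics will be summarised with frequencies and proportions") or the unspecified baseline predictors in the multiple imputation. That too stands: the score is named in no analysis, which is not proof that it is used in none. The covariate list of the logistic models, however, is stated in full.

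Severity is not wholly ignored either. ASA score is recorded, and the form described in "Immediately after index operation, the surgeon fills out the baseline form containing patient characteristics, Charlson comorbidity index" also holds the Mannheim index. Neither is in the covariate list.

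Finally, SOFA is listed only under postoperative monitoring in the data-collection section, so complete capture of the preoperative score is not assured, and the main analyses are complete-case. This is a fair caution, and the fix has to deal with it.

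**Conclusion.** The point holds for the adjusted complication models: their covariate list is fixed without any measure of acute organ dysfunction, although one is taken before surgery. The consequence is lost precision and weaker protection against chance imbalance. The 16% to 49% fall in variance applies only to a continuous outcome and only under the assumed correlation of 0.4 to 0.7. The primary chi-square test is not biased by the omission, and 340 stands.

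Stronger readings are not supported:
- A reader might infer that the plan fixes a Wilcoxon rank-sum test, which takes no baseline, for the seven-day SOFA outcome. That sentence closes the paragraph on patient characteristics. The article states no method for the SOFA and CRP outcomes, and one may stand in an analysis plan that is not shown.
- A reader might infer that postoperative CRP largely reflects its preoperative level. Nothing in the documents shows this.
- A reader might infer that the per-protocol comparison is confounded by preoperative organ dysfunction, since VAC may be applied against allocation. The documents do not show that preoperative SOFA drives those departures, so the conclusion does not rest on this.

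**What to change.** 1. In Statistical analysis, add preoperative SOFA to the prespecified covariates of the adjusted logistic models, beside age, performance status and comorbidity.
2. In Data collection and participant timeline, list it among the pre- and perioperative baseline data, so that this section agrees with Preoperative patient assessment.
3. State that wherever postoperative SOFA is compared between groups, the preoperative score is the baseline covariate.
4. State that missing preoperative scores are imputed as a baseline covariate, so that no patient leaves a complete-case adjusted model for lack of the score.

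The cost is wording and, if the score is not yet entered in the trial database, one data field. No new assessment is needed, because the article already has the score taken. The primary test and the sample size remain as they are.
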